#### Primary analyses

The primary analyses will be conducted on an intention-to-treat basis. The focus will be on estimation of the effect [31] at 2 years, but hypothesis tests will also be conducted. Between-group comparisons will be conducted using a linear model in which the outcome is a linear function of a dummy-coded variable representing group membership (stabilization surgery or control group) and baseline score [32]. For the outcomes of pain and functional impairment, participant-reported improvement and incidence of shoulder dislocations, all of which are measured at baseline and 6, 12 and 24 months, mixed models will be used. The mixed models will incorporate a random intercept for subject. A negative binomial model will be used to analyze data on the incidence of dislocations. A sensitivity analysis will be conducted in which multiple imputation is used to account for missing data [33, 34].

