**Methods/Design:**

140 participants will be recruited. Patients with feelings of insecurity (apprehension) at their shoulder joint, which is not the result of a collision injury, with physical signs of shoulder joint instability will be invited to participate. Consenting participants will undergo arthroscopic investigation of the shoulder joint. Patients with capsulolabral damage will be randomly allocated using a concealed allocation procedure to either stabilization surgery immediately following the arthroscopic examination or no additional surgical procedure. All participants will then receive the same postoperative physiotherapy protocol for up to 6 months. Outcomes (pain, functional impairment and number of shoulder dislocations sustained) will be evaluated prior to surgery and, together with participant-reported improvement, again at 6, 12 and 24 months after randomization. The primary endpoint will be pain and functional impairment at 2 years. Participants, clinical staff (but not surgeons) and assessors will be blind to whether stabilization surgery was performed. Data analysis will be conducted on an intention-to-treat basis with the focus on estimation of the effect.

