### Interventions

140 participants will be recruited and randomly allocated to either a:stabilization surgery group (70 participants). Participants in this group will receive an arthroscopic investigation of the shoulder joint followed by arthroscopic stabilization surgery and postoperative physiotherapy rehabilitation.control group (70 participants). Participants in this group will receive an arthroscopic investigation of the shoulder joint followed by postoperative physiotherapy rehabilitation.

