### Sample size

The sample size was calculated assuming a 10.4% change on the WOSI given a standard deviation of 18% change, a significance level of 5% and assuming a 10% (worst-case) loss to follow-up. A 10.4% change in total WOSI score represents the minimally important change required to represent a clinically significant improvement [28]. This is a conservative sample size estimate as it ignores the additional power conferred by the longitudinal analysis that is to be used in this study.

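### The primary target is the WOSI effect at 2 years, but the model terms stated, taken literally, estimate the average effect over 6, 12 and 24 months

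*Protocol article*

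**What the plan says.** The target is stated twice. The Abstract (Methods/Design) says "The primary endpoint will be pain and functional impairment at 2 years". The section Primary analyses opens its modelling text with "The focus will be on estimation of the effect [31] at 2 years, but hypothesis tests will also be conducted".

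The same section then describes the model in three steps:

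- The arms are compared by regression with two named terms: "the outcome is a linear function of a dummy-coded variable representing group membership (stabilization surgery or control group) and baseline score".
- The next sentence turns to WOSI, participant-reported improvement and dislocations, "all of which are measured at baseline and 6, 12 and 24 months, mixed models will be used".
- One further feature is given: "The mixed models will incorporate a random intercept for subject".

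The section Sample size calls its estimate conservative because "it ignores the additional power conferred by the longitudinal analysis that is to be used in this study".

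**The concern.** Group and baseline score are the only regressors named, and the random intercept is the only feature added for repeated data. A statistician who programs exactly that obtains one group coefficient shared by all follow-up visits. It cannot be a 2-year effect unless the effect is the same at 6, 12 and 24 months.

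The article gives no ground for assuming a constant effect. Study objectives hypothesises benefit in both the short and the long term but does not say that the two are of equal size. The Background raises the possibility that surgery does harm later on. Physiotherapy ends by six months, so the first follow-up visit falls at the end of the treatment that both arms share. An early effect that fades and a late effect that emerges are both plausible, and the trial should be able to tell them apart.

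Under the literal model, a fading effect could be reported as a 2-year benefit and a late effect would be understated.

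**Working it through.** **Inputs from the article.** Sample size states "assuming a 10.4% change on the WOSI given a standard deviation of 18% change, a significance level of 5% and assuming a 10% (worst-case) loss". Interventions gives 70 per arm.

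**Assumptions.** The article gives none of the following:
- two-sided testing;
- SD 18 at each visit;
- within-patient correlation ρ = 0.6, with 0.3 to 0.7 as a range;
- the effect trajectories;
- 63 complete patients per arm;
- no baseline adjustment, except in the simulation.

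**1. The plan's own figure.** n per arm = 2 × 18² × (1.960 + 1.282)² / 10.4² = 62.95, so 63. Allowing for 10% loss, 63 / 0.9 = 70 per arm, or 140. The stated total is reproduced at 90% power, which the article does not itself state (80% would give 108 and 85% would give 120). The sample size is not at fault.

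**2. What the single coefficient estimates.** A random intercept implies the covariance V = σ²[(1−ρ)I + ρJ] over the three visits, where J is the matrix of ones. The generalised least-squares weights are proportional to V⁻¹1, which is proportional to a vector of ones. Each visit therefore gets weight 1/3, whatever ρ is. With complete data, adding a visit main effect alone leaves the coefficient unchanged.

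**3. Standard errors at ρ = 0.6.**
- Averaged effect: √[2 × 18² × (1 + 2 × 0.6) / (3 × 63)] = 2.75.
- 24-month contrast: 18 × √(2/63) = 3.21.

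**4. Consequences.** Power = Φ(expected estimate / SE − 1.96).

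| True effect at 6 / 12 / 24 months | Expected estimate, averaged | Chance of p<0.05, averaged (ρ = 0.6) | Range for ρ = 0.3 to 0.7 | 24-month contrast |
|---|---|---|---|---|
| 10.4 / 10.4 / 0 | 20.8 / 3 = 6.93 | 71% | 84% to 68% | 5% (no effect) |
| 4 / 8 / 10.4 | 22.4 / 3 = 7.47 | 78% | 89% to 74% | 90% |

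The ranges use averaged SEs of 2.34 at ρ = 0.3 and 2.87 at ρ = 0.7.

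**5. Simulation check** (150 runs per scenario, 63 per arm, SD 18, ρ = 0.5, baseline as covariate).
- True effects 10.4 / 5.2 / 0: the literal model gave a mean estimate of 5.2 and rejected in 69% of runs. With visit and group-by-visit terms, the 24-month contrast gave −0.1 and rejected in 3%.
- True effects 0 / 5.2 / 10.4: 5.2 and 71% for the literal model, against 10.3 and 97% for the 24-month contrast.
- Constant 10.4: both target the same value (10.4 and 10.2).

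**6. Random intercept alone, with group-by-visit terms added.** The 24-month SE is then built from the mean of the three visit variances.
- Assumed SDs 15 / 17 / 20: model SE √(2 × 304.67 / 63) = 3.11 against a true 20 × √(2/63) = 3.56. Type I error is 2 × [1 − Φ(1.96 × 3.11/3.56)], about 8.7%.
- Assumed SDs 20 / 18 / 16: 3.22 against 2.85, about 2.7%.

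The direction depends on SDs that the article does not give.

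**The case against.** The strongest reply is that the criticised model has to be assembled. The sentence on group and baseline reads as a template for all outcomes. It fits rotation range and strength, which are re-assessed only at 6 months. It cannot be complete for dislocations, which get a negative binomial model. The mixed-model sentences do not restate fixed effects, and the stated focus on 2 years suggests that a time-specific contrast is meant. Visit coding and covariance structure are commonly left to an analysis plan.

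Much of this stands: a 24-month contrast may well be intended, and the text does not prove otherwise. But the article does more than leave the model open. It states the predictors and the random effect, and those terms do not deliver the estimand stated beside them unless the effect is constant.

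A reader might infer more than the text supports:

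- **That baseline WOSI also enters as a response and dilutes the effect.** The article makes baseline score a regressor; listing baseline among the measurement times describes data collection.
- **That the random intercept inflates type I error.** It may, or it may make the test conservative; nothing in the article favours either.
- **That the claim of additional power is wrong.** Baseline adjustment can add precision, and earlier visits can recover some of what dropout loses. Only a gain from averaging visits conflicts with a 2-year target.

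**Conclusion.** The point holds as a mismatch between the stated estimand and the stated model terms. It does not show that the investigators intend to analyse an average. The equal weighting is algebra and needs only complete data and a random intercept. The size depends on the assumed trajectory and correlation. In the two main examples at ρ = 0.6, there is about a 71% chance of a significant result with no 2-year benefit, or a fall in power from 90% to 78% with the estimate at 7.5 instead of 10.4. If the effect is constant from 6 to 24 months, there is no bias. Because this is the trial's primary estimate and test, the wording should be settled before any unblinded result is seen. The covariance choice is a lesser matter of unknown size and direction.

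**What to change.** In Primary analyses, state that:

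- the responses are WOSI at 6, 12 and 24 months, with baseline WOSI as covariate only;
- the fixed effects include group, categorical visit and group-by-visit;
- the primary estimate and test is the group difference at 24 months, with 6 and 12 months secondary.

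Analysis of covariance of the 24-month score is a simpler alternative. If the mixed model is kept, an unstructured within-subject covariance is preferable to the random intercept alone, so that the 24-month standard error rests on the 24-month variance. Three visits need six covariance parameters, which about 126 completing patients (2 × 63) can support.

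In Sample size, keep the sentence on additional power but attribute the gain to baseline adjustment and recovery of information lost to dropout.

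The cost is wording only, with no extra patients or data. What is given up is any precision from averaging visits: at ρ = 0.6, an SE of 2.75 against 3.21 for the 24-month contrast, before baseline adjustment.

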## Methods/Design

### Design

A two-arm, double-blind randomized controlled clinical trial will be conducted. 140 patients will be recruited in two study centres and will undergo a clinical assessment to assess potential eligibility for the study. Potentially eligible patients who consent to participate will undergo arthroscopy and those with arthroscopic evidence of capsulolabral damage will be randomly allocated during the procedure into one of two groups: a *stabilization surgery* group and a *control* group. The primary outcome (pain and functional impairment) and secondary outcomes (participant-reported improvement and number of shoulder dislocations sustained) will be evaluated at baseline and 6, 12 and 24 months after randomization. Additional secondary outcomes of shoulder rotation range of motion and strength will be evaluated at 6 months after randomization. Ethics approval to conduct this study has been granted by the NRES Committee London-Stanmore and NRES Committee Wrightington, Wigan and Leigh.

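### With only a random intercept specified, the 2-year WOSI interval and p-value are miscalibrated if residual variance at 24 months differs from the average over visits

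*Protocol article*

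**What the plan says.** The Design section has the primary outcome, the WOSI, measured repeatedly: it "will be evaluated at baseline and 6, 12 and 24 months after randomization". The Primary analyses section sets the target: "The focus will be on estimation of the effect [31] at 2 years, but hypothesis tests will also be conducted". The Abstract likewise places the primary endpoint at 2 years, and the Interim analysis section sets the final test at p < 0.05.

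For the model, Primary analyses makes the outcome a "linear function of a dummy-coded variable representing group membership (stabilization surgery or control group) and baseline score". For the repeatedly measured outcomes, "all of which are measured at baseline and 6, 12 and 24 months, mixed models will be used". The one statement about covariance is: "The mixed models will incorporate a random intercept for subject". No random slope, residual structure, robust standard error or sensitivity analysis for the covariance is named. The only sensitivity analysis named is multiple imputation for missing data. No visit or group-by-visit term is stated.

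**The concern.** A linear mixed model whose only covariance element is a random intercept has independent residuals with a single variance. It therefore assumes the same total variance at every follow-up visit and the same correlation between every pair of visits (compound symmetry). That matters little for an average over visits. It matters more when the wanted quantity is the group difference at one visit, because the model judges the precision of the 24-month difference by a variance pooled over all three visits.

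Unequal residual variance is plausible in this design even if the raw WOSI spread never changes. The baseline score is a covariate, so the residual variance at a visit is the raw variance times (1 − r²), where r is the correlation between baseline and that visit. If r fades between 6 and 24 months, the residual variance grows. At stake is the calibration of the trial's main interval and test: too many false positives if the variance rises, lost precision if it falls.

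**Working it through.** **Inputs from the protocol article**
- Sample size section: "The sample size was calculated assuming a 10.4% change on the WOSI given a standard deviation of 18% change", with "a significance level of 5% and assuming a 10% (worst-case) loss to follow-up".
- Interventions section: 70 participants per arm, 140 in total.
- Not stated: power, sidedness, SDs by visit, correlations. Two-sided testing is assumed. All visit-specific values below are assumptions.

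**Step 1. Reproduce the plan's figure**
- n per arm = 2 × (1.960 + 1.282)² × 18² / 10.4² = 2 × 10.51 × 324 / 108.16 ≈ 63.
- Allowing for 10% loss: 63 / 0.9 = 70 per arm, 140 in total.
- 80% power would give 108 and 95% would give 174, so the implied power is 90%. The calculation compares the arms at a single time point and does not use the mixed model, so the covariance question leaves it untouched.

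**Step 2. The standard error under a random intercept**

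Take complete data and group-by-visit terms, with baseline as a covariate.
- Model-based SE at 24 months = √(2 × mean of the three visit variances / n).
- True SE = √(2 × 24-month variance / n). With residual SD 18 and n = 63 this is 18 × √(2/63) = 3.21.
- SE ratio (model/true) = √(mean visit variance / 24-month variance).
- True two-sided error of a nominal 5% test = 2 × [1 − Φ(1.96 × ratio)].

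Worked example, SDs 14/16/18: mean variance = (196 + 256 + 324)/3 = 258.7; ratio = √(258.7/324) = 0.894; error = 2 × [1 − Φ(1.752)] = 8.0%.

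| Assumed residual SD at 6/12/24 months | SE ratio | True error |
|---|---|---|
| 18/18/18 | 1.000 | 5.0% |
| 16/17/18 | 0.946 | 6.4% |
| 14/16/18 | 0.894 | 8.0% |
| 12/15/18 | 0.844 | 9.8% |
| 20/19/18 | 1.057 | 3.8% |
| 22/20/18 | 1.115 | 2.9% |

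Simulation at 63 per arm (20,000 runs each) agrees: 8.1–8.4% for 14/16/18, 10.3% for 12/15/18 and 2.8–2.9% for 22/20/18.

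**Step 3. Constant raw SD, fading baseline correlation**

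With r = 0.6/0.5/0.3 and a baseline slope fitted per visit, the residual variances in units of the raw variance are 1 − 0.36 = 0.64, 1 − 0.25 = 0.75 and 1 − 0.09 = 0.91. The mean is 0.767, the ratio √(0.767/0.91) = 0.918 and the error 7.2%. A REML simulation (140 patients, one baseline slope, group-by-visit terms, 10% missing at 24 months, 4,000 runs per case) gave 7.5% for this case and 6.8% for r = 0.5/0.4/0.3. A control with constant r = 0.4 and equal correlations gave 4.9%.

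**Step 4. Unequal correlation between follow-up visits alone**

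Hold the SDs equal and let the correlations (6–12, 6–24, 12–24 months) be 0.8/0.5/0.7 or 0.8/0.3/0.5. With complete data the ratio is 1.00 and the error 5.0%. With 10% dropout the ratio is 0.987–0.991 and the error 5.2–5.3%.

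**Step 5. One common group effect, no group-by-visit term**

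Simulated error stays at 5.1–5.4% under every structure tried. The quantity estimated is then an average over visits, not the effect at 2 years.

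**The case against.** The strongest objection is that the text does not restrict the covariance to a random intercept. It says the models will incorporate one. A random intercept can sit alongside visit-specific residual variances or robust standard errors, and an article commonly leaves such details to a full protocol or SAP, neither of which is shown. This stands to the extent that a reader might infer that the plan permits nothing else; the document does not say so. But the article does choose one covariance element, and its ordinary reading is compound symmetry.

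A second objection is that the distortion appears only once group-by-visit terms are added, and the article does not state them. Taken literally, with one group effect, the standard error is sound. That is correct (Step 5), but that reading does not deliver the stated 2-year effect. Any version that targets 24 months meets the variance problem.

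A third is that no figure in the document shows WOSI variance changing over follow-up, so every size is assumed. This stands in full. The direction of the error is also unknown.

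A reader might further infer that the 2-year p-value is wrong unless both equal variance and equal correlation hold. Step 4 does not support that: unequal follow-up correlation alone leaves the standard error right with complete data and about 1% off at the planned 10% loss.

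**Conclusion.** The point holds as a conditional one. If the WOSI model is fitted with a random intercept, independent equal-variance residuals and model-based standard errors, and the 24-month effect is read from group-by-visit terms, then the 2-year interval and p-value are miscalibrated whenever the 24-month residual variance differs from the three-visit average. In the scenarios tried, the true error of a nominal 5% test is about 6–10% if residual variance rises to 24 months and about 3–4% if it falls. In the SD scenarios tabulated, the standard error is about 5–16% too small in the first case and 6–12% too large in the second. These figures rest on assumed SDs and correlations, because the document gives a single SD of 18%.

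The document does not show that the planned analysis will be wrong, or that its error rate will be inflated and not deflated. The sample size of 140 is unaffected. The argument concerns the linear model for the WOSI and does not carry over to the negative binomial model for dislocations. It is an inexpensive improvement to a stated model choice, not a defect that threatens the trial.

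**What to change.** In the Primary analyses section, or in the SAP if it is still open, specify for the WOSI:
- fixed effects for group, visit, group-by-visit, baseline score and baseline-by-visit;
- an unstructured residual covariance over 6, 12 and 24 months in place of the random intercept, fitted by REML with Kenward-Roger degrees of freedom;
- the 2-year estimate, interval and test taken from the 24-month contrast of that model;
- a random intercept with robust standard errors as the named fallback if the model does not converge.

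The cost is a few lines of text. The covariance has six parameters instead of two, which 140 participants support, and there is a slight loss of efficiency if the variances are in fact equal. Data collection and sample size do not change. Fixing the structure in advance also removes the option of choosing it after seeing the data.

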### Statistical analyses

#### Interim analysis

One interim analysis of efficacy will be conducted when 50% of the estimated sample has completed one year follow-up assessment. The decision to continue the trial or stop the trial early will be made by the Trial Management Group and Steering Group, informed by an analysis of the Haybittle-Peto boundary [30]. The p-value threshold for this interim analysis will be set at 0.001. The final analysis will be evaluated at the significance level specified in the sample size calculation i.e. p < 0.05.

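### The only missing-data sensitivity analysis named, multiple imputation, specifies no departure from missing at random; in its standard form it would largely repeat the primary 24-month WOSI result

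*Protocol article*

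**What the plan says.** The Primary analyses section of the protocol article plans an intention-to-treat comparison and sets the target: "The focus will be on estimation of the effect [31] at 2 years, but hypothesis tests will also be conducted". For WOSI, perceived effect and dislocations it states "all of which are measured at baseline and 6, 12 and 24 months, mixed models will be used", and then "The mixed models will incorporate a random intercept for subject". It names one analysis for missing data: "A sensitivity analysis will be conducted in which multiple imputation is used to account for missing data".

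That sentence carries two literature references but gives no missingness mechanism, no list of imputation variables and no departure to be examined. The phrase missing at random occurs nowhere in the article. The Sample size section plans for limited loss, "assuming a 10% (worst-case) loss to follow-up".

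**The concern.** A sensitivity analysis is informative when it changes the assumption that the primary result depends on. A likelihood-based mixed model gives valid estimates when missingness depends only on what has been observed and modelled: group, baseline score and the earlier WOSI scores. Standard multiple imputation from those variables makes the same assumption, so it should return nearly the same 24-month estimate. A reader of the trial report could take that agreement as evidence of robustness, although the assumption was never varied.

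The untested possibility is that non-response at 24 months depends on the unseen score itself. Patients who do badly may seek care elsewhere, or recovered patients may stop replying. If the size or direction of this differs between arms, the treatment difference is biased. The Discussion section says the trial will settle the referral question definitively, so the report should be able to say how strong such dropout must be to change the conclusion.

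**Working it through.** **Inputs from the protocol article.** Sample size section: WOSI change 10.4, standard deviation 18, significance level 5%, loss 10%. Interventions section: 70 per arm. Interim analysis section: final test at p < 0.05. Power and sidedness are not stated.

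**Step 1: reproduce the sample size.** With a two-sided 5% level and an assumed power of 90%, n per arm = 2 × (1.960 + 1.282)² × 18² / 10.4² = 63 after rounding up. Allowing for loss, 63 / 0.90 = 70 per arm, or 140 in total, which matches the plan. Two-sided power of 80%, 85% or 95% would give 108, 120 or 174.

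**Step 2: significance limit at the planned loss.** SE = 18 × √(2/63) = 3.21. The smallest significant difference is 1.96 × 3.21 = 6.29, about 6.3 points.

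**Step 3: effect of a departure.** If missing participants in one arm differ from their imputed values by δ, the difference moves by (missing fraction) × δ.
- δ = 10: 0.10 × 10 = 1.0 point, or 1.0/3.21 = 0.3 SE.
- δ = 20: 0.10 × 20 = 2.0 points, or 0.6 SE.
- Opposite shifts in the two arms double these. Equal shifts with equal loss cancel.

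**Step 4: tipping shift = (observed difference − limit) / missing fraction.** The one-arm value is halved for opposite shifts in both arms.

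| Loss per arm | Limit | Observed difference | One arm | Opposite, both arms |
|---|---|---|---|---|
| 10% (plan) | 6.29 | 10.4 | 4.11/0.10 = 41 | 21 |
| 10% (plan) | 6.29 | 8 | 1.71/0.10 = 17 | 9 |
| 10% (plan) | 6.29 | 7 | 0.71/0.10 = 7 | 4 |
| 20% (assumed) | 6.67 | 10.4 | 3.73/0.20 = 19 | 9 |

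The last row uses 70 × 0.80 = 56 analysed per arm and SE = 18 × √(2/56) = 3.40. A 20% loss is twice the article's stated worst case and is shown only as a range. These are approximations: the SE is the unadjusted two-group one from the sample-size inputs and is held fixed as δ varies.

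**Step 5: does standard imputation differ from the mixed model?** A simulation on assumed, deliberately adverse inputs used 70 per arm, a true effect of 10.4 and SD 18. All 14 losses (10% of 140) fell in one arm at 24 months, with loss depending on the unseen 24-month score. There were 100 runs per setting. Imputation used group and the earlier WOSI scores.

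| Within-person correlation | Full data | Mixed model | Multiple imputation |
|---|---|---|---|
| 0.3 | 10.8 | 14.6 | 14.7 |
| 0.5 | 10.3 | 13.2 | 13.2 |
| 0.7 | 10.3 | 11.9 | 12.0 |

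The two methods agreed on average within about 0.1 point, with a mean absolute difference of about 0.26 per run. Both were biased by about 1.6 to 3.8 points, which is 15% to 37% of 10.4 (1.6/10.4 and 3.8/10.4). In this scenario the planned check would have appeared to confirm the primary result.

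**The case against.** A reader might infer that the planned imputation definitely assumes missing at random and therefore cannot reveal any dropout bias. The article does not support that. It never states the assumption, and imputation can also be run under missing not at random; the delta adjustment proposed here is itself multiple imputation and compatible with the article's sentence. The imputation model is detail that an article commonly leaves to a fuller document, so its absence is no error.

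Imputation may also add information. Perceived effect and dislocations at 6 and 12 months, and rotation range and strength at 6 months, are not in the WOSI model. Patients heading for a poor result may already show it there. For range and strength, measured after randomization only at 6 months, there is no repeated-measures model and imputation is not redundant.

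The impact is modest under the plan's own assumptions. At 10% loss and an effect of 10.4, a 20-point departure in one arm leaves 8.4 points, above the limit. Participants, physiotherapists and assessors are blinded and aftercare is the same in both arms, which makes allocation-driven dropout less likely. The simulation is extreme in placing every loss in one arm.

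All of this stands and limits the point. What remains is that the article does choose its one missing-data sensitivity analysis and attaches no departure to it. Imputation with auxiliary variables is still a missing-at-random analysis unless a departure is specified. Blinding does not prevent dropout driven by outcome, and if surgery changes outcomes, such dropout can differ by arm.

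**Conclusion.** The point holds in a limited form and is worth acting on. If the imputation is of the standard kind and uses much the same variables as the mixed model, its agreement with the 24-month WOSI result says little about outcome-related dropout. That condition is inferred from usual practice; the article does not state it.

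The size depends on the result obtained. At the planned loss, a result near the design effect is safe against plausible departures, and it would be wrong to infer that the 2-year conclusion is generally fragile. A result only a point or two above the significance limit could be reversed by departures within 20 points. Loss beyond the plan would bring even the design effect within reach of a departure of that size. These figures rest on the article's SD of 18, the unadjusted standard error and equal loss in the two arms. The simulated bias rests on assumed inputs and illustrates the mechanism; it is not a forecast for this trial.

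**What to change.** Keep the planned multiple imputation and make three changes before unblinding:

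- State the missingness assumption of the mixed model and of the imputation.
- Include auxiliary outcomes in the imputation model: perceived effect and dislocations, and the 6-month rotation range and strength.
- Add a pre-specified delta adjustment. Shift imputed 24-month WOSI values by 0, 5, 10, 15 and 20 percentage points, separately by arm and in opposite directions. Report the shift at which the 24-month conclusion changes, or that none in the range does.

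The grid is wide enough to be informative. At 10% loss its extreme, 20 points in opposite directions, moves the effect by 0.10 × 40 = 4.0 points. That is just short of the 4.11 points of slack at an observed 10.4, and well beyond the slack at 7 or 8.

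The cost is a little more analysis code on an imputation already planned. No new data or participants are needed, and the primary analysis is unchanged.
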